### Blinding/masking

2.6

The acupuncturist will only be responsible for acupuncture treatment. The duration, acupoints, and date of the acupuncture treatments will be recorded in the EDC system when the treatment is finished. The RF_CSA_, MRC-SS and clinical outcome data will not be visible to the acupuncturist.

The RF_CSA_ and MRC-SS measurements will be assessed separately by individual physicians. Another intensivist will perform a spot-check on the RF_CSA_ measurements, and a neurologist will check the MRC-SS measurements at a fixed time point. At the end of the study, a consistency test will be performed on the measurements. Neither the intensivist nor the neurologist will be able to access the measured value of the other assessment, and the assessors will not know the specific acupuncture treatment or other outcome indicators.

Subjects will know their group assignment. Acupuncturists and critical care providers will also know the group assignments of the subjects during treatment. The data analyst will only know that there are 2 groups, but the specific group assignments will be blinded. Because this study is a prospective pragmatic controlled trial (pCT), only the outcome assessors and data analysts will be blinded; blinding will have no effect on the subjects, so there is no need for the study to be unblinded.

### Study groups

2.7

Since this study is a real-world study, the grouping of the study subjects was determined by the actual observations. Therefore, no randomization of groups was set in this study. The subjects will be as allocated into 2 arms.

Group 1: acupuncture group

When the participant meets the inclusion criteria (1 to 5), the acupuncturist will assess the conditions for patient treatment. Patients can enter this group and have acupuncture treatment if they do not have specific conditions (such as edema, coagulopathy, acupoints local skin and soft tissue infection, and rejection of acupuncture treatment) that are not suitable for acupuncture.

Group 2: control group

Patients who are not suitable for acupuncture or are not willing to receive acupuncture could enter this group. In addition to basic treatment, patients in this group will be prescribed exercises, such as early in-bed activities or wheelchair activities.

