#### Acupuncture treatment

2.5.1

According to the patient's (and/or their relatives’) willingness and the clinical routine, a group of physicians will assess the acupuncture treatment within 24 hours in patients who meets the inclusion criteria 1 to 5. All physicians are required to have at least 3 years (or 300 hours) of practical experience with acupuncture. The acupuncture treatment will be performed by stainless steel needles (0.30 mm × 40 mm; 0.30 mm × 25 mm; Suzhou Medical Supplies Factory Co., Ltd., Suzhou City, China). The acupuncture treatment will be performed by the technique of lifting, thrusting, twirling and rotating the needle until the patient is being “De-qi” (getting a numbness or other acupuncture feeling). Two points that do not cross the joint will be chosen for electrical stimulation. The needle will be kept in place for approximately 30 minutes. By the time we remove the needles, a clean cotton balls will be pressed to the skin to prevent bleeding.

All patients must be treated at “3 obligatory basic acupuncture points”: ST36, ST40 and LI10. Furthermore, at least 3 additional acupuncture points will be selected according to the principles of traditional Chinese medicine (for example, if the patient has a mental disorder manifestation, acupoints such as GV20, GV24, and EX-HN3 can be added to promote the patient's waking). Additional acupoints could be applied, and ear acupuncture points might also be included. All acupoints selected in each session will be recorded. A traditional Chinese syndrome diagnosis is required, and the diagnosis will be documented. Acupuncture treatment will be performed twice a day and lasts for 30 minutes. If the included subjects do not meet the exclusion criteria and do not terminate their participation in study, they will receive acupuncture treatment during their entire ICU stay. If the patient is discharged from the ICU, the acupuncturist will continue to follow the patient until the 14-day acupuncture session is completed. Both the acupuncture group and the control group will receive basic sepsis treatment. The selection of acupuncture points is listed in Table 1.

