### Statistical analysis

2.10

All available data will be analyzed descriptively. For continuous data, the normality test will be applied at the very beginning of the analysis. We will bewrite the results as the means, standard deviations, and 95% confidence intervals (CIs) for continuous data that conform to the normal distribution; medians, quartiles, and ranges for rank data and continuous data that do not fit the normal distribution; and percentages for discrete data.

The change in the RF_CSA_ from baseline will be analyzed by a generalized additive mixed model of repeated measures design. Analysis of the time-to-event outcome (at day 28, day 90, six months, and 1 year after the admission of ICU) will be conducted by applying Kaplan-Meier curves. Kaplan-Meier survival curves will be performed to describe the survival rate between the 2 groups, and the log-rank method will be used to compare the survival rates of the acupuncture group and control group. Multivariate Cox proportional hazard regression models will be used to analyze several constituents (such as acute physiology and chronic health evaluation-II, SOFA score, demographic and diagnostic data), adjust for covariates, and correct for confounding. Our team will use similar approach mentioned above to analyze secondary outcome measures when they can be expressed as time-to-event outcome dimensions. All regression analyses (generalized additive mixed models, log-rank analysis, multivariate Cox proportional hazard regression models) will include the same covariates as the primary analysis. If there are any measurable differences between the 2 study groups with regard to prognostic factors, a propensity score analysis will be applied to assess the sensitivity of the results to any treatment allocation biases. The propensity score will be set for the main outcome. After the 2 sets of data are analyzed according to the previous analysis, the patients will be matched with the propensity score, and then the main outcomes of the matched 2 groups will be compared again to see if there are any similarities or differences between the 2 groups before and after the match. If they are the same, the results are stable; however, a difference means that there are factors affecting the evaluation of the outcome before the match, and these factors will need to be explained.

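### Patients with contraindications to acupuncture are controls by rule, and the adjustment described in the protocol does not make the full groups comparable

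*Protocol article*

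**What the plan says.** The Study groups section states: "Therefore, no randomization of groups was set in this study". Group membership follows two rules.

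- Acupuncture group: "Patients can enter this group and have acupuncture treatment if they do not have specific conditions (such as edema, coagulopathy". The list goes on to local skin and soft tissue infection at the acupoints and to refusal of acupuncture.
- Control group: "Patients who are not suitable for acupuncture or are not willing to receive acupuncture could enter this group".

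The Acupuncture treatment section adds that willingness and routine practice play a part: "According to the patient's (and/or their relatives’) willingness and the clinical routine, a group of physicians will assess the acupuncture treatment within 24 hours".

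None of edema, coagulopathy or infection at the acupoints appears among the exclusion criteria.

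For adjustment, the Statistical analysis section plans Cox models with covariates "such as acute physiology and chronic health evaluation-II, SOFA score, demographic and diagnostic data), adjust for covariates, and correct for confounding". The other regression analyses are to use the same covariates. The propensity score is conditional: "If there are any measurable differences between the 2 study groups with regard to prognostic factors, a propensity score analysis will be applied". It is introduced there to test sensitivity to allocation bias, and its form is matching: "the patients will be matched with the propensity score, and then the main outcomes of the matched 2 groups will be compared again". The abstract and Design section call the trial propensity-score stratified.

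**The concern.** A patient with a listed contraindication can only be a control. This goes beyond ordinary confounding: for these patients the probability of acupuncture is zero by rule (a positivity violation), so no treated patient exists with whom to compare them. Left in the effect estimate, they mix the effect of acupuncture with the effect of not having a contraindication.

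The objective is causal: whether acupuncture affects muscle area, strength and long-term prognosis. One primary outcome is time to death or unplanned ICU readmission for invasive ventilation, and coagulopathy or added infection is a plausible marker of risk in sepsis. The results are also meant to inform a multicenter study, so a bias here would be carried forward.

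**Working it through.** **1. The passages side by side.** Contraindicated patients are barred from acupuncture, admitted as controls and not excluded. The named covariates are APACHE II, SOFA, demographic and diagnostic data. Suitability, edema and infection at the acupoints are not among them. The text on screening data lists coagulation function and infection site, but not edema or acupoint infection; the data-collection table is not shown, so it cannot be said that they go unrecorded. Refusal sits in the same list as the medical conditions: "specific conditions (such as edema, coagulopathy, acupoints local skin and soft tissue infection, and rejection of acupuncture treatment". Unless the two are separated at recording, an unsuitable control cannot be told from an unwilling one.

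**2. The plan's own sample size.** Two proportions, 0.125 and 0.393, two-sided alpha 0.05, power 0.80, unpooled variance:

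n = (1.960 + 0.842)² × (0.125×0.875 + 0.393×0.607) / 0.268² = 38.02, rounded up to 39 per group.

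The step to 49 fits 20% dropout (39/0.80 = 48.75), a rate the protocol does not state. The figure reproduces. It makes no allowance for confounding.

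**3. Crude false gap with zero effect.** Assumed inputs: event risk 25% in suitable patients (treated or not), 50% in unsuitable patients, and a share f of controls unsuitable.

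Control risk = f×0.50 + (1−f)×0.25, so gap = f×0.25.

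| f | Control risk | Acupuncture risk | Gap | Risk ratio |
|---|---|---|---|---|
| 10% | 27.5% | 25% | 2.5 points | 0.91 |
| 30% | 32.5% | 25% | 7.5 points | 0.77 |
| 50% | 37.5% | 25% | 12.5 points | 0.67 |

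If unsuitable patients have the same risk as the rest, the gap is zero at every share.

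**4. Chance of a false significant benefit, 49 per group, zero effect.** Assume a suitable-patient risk of 20% to 30%, unsuitable patients at 1.5 to 2 times that, and half of controls unsuitable. The chance is 9% to 33%, against a nominal 2.5% in the favourable direction. This too is a crude comparison.

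**5. Does adjustment for severity remove it?** Simulation with a continuous outcome, zero effect, 49 per group, 3,000 runs. Assumptions: unsuitability costs 0.5 residual SD beyond measured severity, severity is itself 0.5 SD higher in unsuitable patients, the severity slope is −0.4, and half of controls are unsuitable. Expected crude gap: 0.5 × (0.5 + 0.4×0.5) = 0.35.

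| Analysis | Mean false benefit (SD) | Significant in favour |
|---|---|---|
| Crude | 0.35 | 33.1% |
| Adjusted for severity | 0.24 | 20.5% |
| Adjusted for severity and unsuitability | about 0 | 2.5% |
| Suitable patients only, adjusted for severity | about 0 | 2.7% |

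If every control is unsuitable, severity adjustment leaves 0.50 SD (significant in 67%) and the last two analyses cannot be fitted.

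**The case against.** A reader might infer that no adjustment could ever make these groups comparable. The documents do not support that. The control rule also admits patients who are suitable but unwilling, and these do have treated counterparts. For the effect in treated patients, matching on a score that contains suitability would leave contraindicated controls unmatched. Steps 4 and 5 of the check agree in part: severity alone fails under the assumptions made, but conditioning on suitability or restricting to suitable patients works. This objection stands and limits the point to the full groups under the analysis as described.

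A reader might also infer that the bias must favour acupuncture on mortality, or that edema distorts the ultrasound muscle area. Both are plausible; neither is shown. APACHE II and SOFA would absorb part of any risk difference. Inclusion criterion 6 requires survival of the ICU stay, which may remove part of an early mortality gap. Controls are also prescribed exercises. Muscle area is analysed as change from baseline, so stable edema would partly cancel.

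The covariate list is open-ended and an analysis plan may complete it. The study is a declared non-randomised pilot, and its authors acknowledge allocation bias. This has some weight, but the allocation rule is fixed in the protocol. If suitability is not recorded prospectively for controls, a later plan cannot reliably recover it. Forgoing randomisation also does not require contraindicated patients in the effect estimate.

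**Conclusion.** The point holds in limited form. As written, the plan puts patients who could never be treated into the control side of the comparison, and neither the named covariates nor the conditional matching deals with this. A false group difference follows if the contraindications carry prognostic weight beyond the covariates used. That is likely, but the protocol does not quantify it. The 2.5 to 12.5 points are correct arithmetic on assumed shares and risks for an unadjusted comparison. They show that the bias could be material and do not estimate it. The defect can be repaired provided enough suitable but unwilling controls exist, a number the protocol does not give.

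**What to change.** 1. For every patient meeting inclusion criteria 1 to 5, record the acupuncturist's suitability assessment, which the protocol already describes, and the reason for non-treatment, before the group is set. Keep unsuitable and unwilling as separate entries, and assess suitability in patients who decline as well.
2. Make the primary comparison among patients judged suitable: acupuncture against suitable but unwilling, with the planned covariate and propensity adjustment.
3. Report unsuitable patients descriptively, and keep the all-controls comparison as a sensitivity analysis.
4. State confounding by willingness as a remaining limitation, since restriction does not remove it.

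The cost is one recorded assessment per patient, amended group wording and fewer controls in the primary comparison. With 49 treated patients, 49×(1−f) suitable controls and equal variances, the interval widens by √{[1 + 1/(1−f)]/2}: about 3% at f = 10%, 10% at 30% and 22% at 50%. The stated 80% power should be restated for the number of suitable controls obtained, rather than enrolment being extended.

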**Methods::**

The ACU-SIM pilot study is a single-center, propensity-score stratified, assessor-blinded, prospective pragmatic controlled trial (pCT) with a 1-year follow-up period. This study will be deployed in a multi-professional critical care department at a tertiary teaching hospital in Guangzhou, China. Ninety-eight intensive care unit subjects will be recruited and assigned to either the control group or the acupuncture group. Both groups will receive basic treatment for sepsis, and the acupuncture group will additionally receive acupuncture treatment. The primary outcomes will be the rectus femoris cross-sectional area, the Medical Research Council sum-score and time-to-event (defined as all-cause mortality or unplanned readmission to the intensive care unit due to invasive ventilation). The activities of daily living will be accessed by the motor item of the Functional Independence Measure. Recruitment will last for 2 years, and each patient will have a 1-year follow-up after the intervention.

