## Introduction

1

Rapid muscle wasting is commonly seen in septic patients during their very first days within the intensive care unit (ICU).^[1,2]^ This phenomenon has been described as sepsis-induced myopathy (SIM),^[3,4]^ one of the most vital components of ICU-acquired weakness.^[4]^ This persistent situation is more common in skeletal muscles and respiratory muscle groups.^[5,6]^ If left untreated, or even the intervention is just delayed, SIM could last for years in survivors of sepsis. SIM can lead to prolonged mechanical ventilation, long-lasting limb motor dysfunction, a protracted in-hospital stay, unplanned readmission and increased long-term mortality.^[7,8]^

At present, there is no targeted treatment for SIM. The efficacy of early rehabilitation (such as in-bed passive/active leg cycling therapy) remains controversial.^[2,9]^ Initiation of these kinds of intervention has barriers in the real world (ie, lack of facilities, personnel and equipment, or the patient cannot fully cooperate with the muscle group exercises).^[10]^ In addition, septic patients may need central venous catheterization and/or invasive arterial monitoring (A-line), not to mention the needs of those who received Intra-aortic balloon pump or extracorporeal membrane oxygenation. All of these factors lead to difficulties in conducting early physical therapy in septic patients. Hence, the development of an easy-to-perform, SIM-targeted treatment is of paramount importance for improving muscle wasting in patients with sepsis.

Acupuncture has been shown to have some advantages in patients with sepsis or muscular diseases separately. However, to the best of our knowledge, no study of acupuncture has been performed or is ongoing in patients with sepsis combined with muscle wasting.

First, several animal experiments have confirmed that acupuncture can improve sepsis by regulating inflammation. Scognamillo-SzabÓ and his colleagues reported that acupuncture can reduce the degree of inflammation during sepsis and effectively curb the development of sepsis.^[11]^ In an LPS-stimulated rat model, pretreatment with acupuncture at ST36 (Zusanli) in septic mice reduced the degree of kidney damage by lowering iNOS levels.^[12]^ In addition, Song JG et al indicated that electroacupuncture preconditioning increased the survival rate by decreasing the pro-inflammatory cytokine concentration.^[13]^

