### Research objectives

1.1

Acupuncture has already been deployed in the treatment of sepsis or muscle weakness. Nevertheless, its efficacy and safety in SIM remains unclear. Therefore, this study has the following research objectives:

(1)To describe the progression of loss of muscle mass (the change of rectus femoris cross-sectional area [RF_CSA]_ from baseline) in patients with sepsis after admission to the ICU and to investigate whether the decline in RF_CSA_ is the morphological basis for muscle weakness in septic patients.(2)To assess whether acupuncture at the Yang-Ming meridian acupoints affects the changes in RF_CSA_ and muscle strength and the long-term prognosis and safety in SIM simultaneously.(3)To serve as pilot research for an upcoming multicenter real-world study.

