#### Basic treatment (Standard of care)

2.5.2

The basic treatment was developed based on the "Surviving Sepsis Campaign: International Guidelines for Management of Sepsis and Septic Shock: 2016”.^[22]^ According to those guidelines, targeted blood glucose range will be set between 8-10 mmol/L (90-144 mg/dL),^[23]^ sedative drugs will be ceased as soon as possible, the use of neuromuscular blockers will be restrain, and early physical exercise will be encouraged.^[23]^

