#### Collecting healthcare data within the ICU stay

2.8.6

During the screening period, the relevant subject information will be completed, and baseline demographic-related items will be collected. The SOFA score, the immediate acute physiology and chronic health evaluation II score (and SAPS score), the GCS score, body temperature, mechanical ventilation or not, the infection site, the pathogenic examination before the administration of antibiotics or use of vasoactive drugs, arterial blood gas analysis, blood routine, coagulation function, liver function, kidney function, heart function, infection index, urine pregnancy test (female subjects), and an electrocardiogram will be recorded during this period. The length of the first antibiotic use and whether the pathogen is sensitive to the antibiotic will be recorded after initiation.

For patients who survive and are discharged from the ICU - meeting all inclusion criteria (1 to 6) - the mechanical ventilation duration time, LOS, total hospital stay, sum sedative analgesic dose, statin dose, blood glucose level, insulin dosage, glucocorticoid dosage, protective constraints, and the duration of neuromuscular blockers will be additionally recorded.

Table 2 shows a general view of the data collecting and the time of acquisition for each item. We will manage all study data anonymously, and all CRFs will be labelled with a study number allocated to each individual participant. The CRF will be in both paper and electronic formats. The paper version of the CRF will be used for backup storage of data and for verification when needed. The daily management of data will be completed on the EDC system. And the details of bedside data collection are shown in Table 3.

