## Discussion

3

SIM is a very serious complication that affects the recovery of septic patients.^[2]^ SIM progressively deteriorates in the early stage of the natural course of sepsis. Approximately 45% to 72% of sepsis patients in the ICU will have voluntary muscle atrophy,^[6,30,31]^ which could lead to a prolonged ICU LOS, unplanned reintubation and mechanical ventilation, unplanned readmission and increased mortality.^[7,8]^ Therefore, SIM has become an important risk factor for increasing mortality and disability of patients with sepsis.

The effects of sepsis on skeletal muscle are multifaceted. Studies have shown that active inflammatory reactions are an important cause of skeletal muscle dysfunction in sepsis.^[32,33]^ Its mechanism may be related to mitochondrial dysfunction caused by an inflammatory reaction.^[34,35]^ Meanwhile, the activity of the proteasome and lysosomal proteolytic system in sepsis patients is increased, leading to increased protein decomposition, which in turn affects skeletal muscle function and induces muscle weakness.^[36]^ MSTN is a new member of the transforming growth factor-β superfamily that has been discovered in recent years; MSTN mainly inhibits muscle growth and metabolism. High expression of MSTN can lead to muscle atrophy.^[11,37]^ In an animal experiment, acupuncture combined with low-frequency electrical stimulation downregulated the expression of MSTN and helped to alleviate muscle atrophy in mice.^[14]^ However, the in vivo expression level of MSTN in SIM patients and its relationship with SIM are not clear.

Previous studies have shown that muscle electrical stimulation therapy and physical therapy have some benefit on SIM.^[12,19,38]^ but the evidence to date is not solid.^[39,40]^ Acupuncture seems to be a promising approach to maintaining muscle mass in septic patients; nevertheless, clinical data specific to the efficacy of acupuncture on SIM are still lacking.

The research objectives of this prospective pCT are to provide preliminary data on the therapeutic, safety and long-term prognosis effects of acupuncture on SIM patients. We are looking forward to proposing a safe and effective method for the treatment of SIM.

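### Section 2.7 prescribes exercise to controls only, so the trial as written compares acupuncture with prescribed exercise, not basic care with and without acupuncture

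*Protocol article*

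**What the plan says.** The abstract (Methods) sets the contrast: "Both groups will receive basic treatment for sepsis, and the acupuncture group will additionally receive acupuncture treatment". Section 2.5.1 repeats that both groups get the basic sepsis treatment. Section 2.5.2 defines that treatment, and within it "early physical exercise will be encouraged", so some exercise belongs to the care of both groups.

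Section 2.7 then describes the two groups. The acupuncture group receives acupuncture if nothing makes it unsuitable; no exercise prescription is mentioned. For the control group it says: "In addition to basic treatment, patients in this group will be prescribed exercises, such as early in-bed activities or wheelchair activities".

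Objective 2 in section 1.1 is worded as a question about acupuncture alone: "To assess whether acupuncture at the Yang-Ming meridian acupoints affects the changes in" rectus femoris cross-sectional area (RF-CSA), together with muscle strength, long-term prognosis and safety.

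**The concern.** If controls are prescribed exercise beyond the shared care and the acupuncture group is not, the groups differ in two treatments. Both are aimed at the same muscle outcomes, two of which are primary: RF-CSA and the Medical Research Council sum-score. The group difference then estimates acupuncture minus the extra benefit of prescribed over encouraged exercise, which is not what objective 2 asks.

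The Discussion gives a reason to take the exercise seriously: "Previous studies have shown that muscle electrical stimulation therapy and physical therapy have some benefit on SIM". It goes on to call the evidence weak, and the Introduction says: "The efficacy of early rehabilitation (such as in-bed passive/active leg cycling therapy) remains controversial". The extra benefit is therefore unknown and may be nil. If it is real, it pulls the apparent acupuncture effect toward zero, and below zero if acupuncture itself does nothing. The study is meant to inform a larger multicentre study, so an unclear contrast would carry forward.

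**Working it through.** **1. The text, side by side**

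| Place | Acupuncture group | Control group |
|---|---|---|
| Abstract, Methods | basic treatment + acupuncture | basic treatment |
| 2.5.1 and 2.5.2 | basic treatment, exercise encouraged | basic treatment, exercise encouraged |
| 2.7 | acupuncture; no exercise prescription stated | basic treatment + prescribed exercise |

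The first two rows agree. The third adds something for controls that neither of the others contains. Because section 2.7 places the prescription on top of basic treatment, the encouragement in section 2.5.2 cannot account for it.

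**2. Can the analysis remove it?** Section 2.10 adjusts for covariates such as severity scores, demographic and diagnostic data, and says "a propensity score analysis will be applied to assess the sensitivity of the results to any treatment allocation biases". These tools address differences that exist before grouping. A control-only prescription starts after grouping and is tied to group, so it forms part of the contrast itself. The co-treatments listed in the text of section 2.8.6 end with "protective constraints, and the duration of neuromuscular blockers will be additionally recorded"; exercise is not among them. Tables 2 and 3 are not shown and may include it.

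**3. The plan's own sample size.** Section 2.3 uses incidences of 12.5% and 39.3%, alpha 0.05 and power 0.80, and states 39 per group. Sidedness is not stated; two-sided is assumed here.

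- Unpooled variance: (1.960 + 0.842)² × (0.125 × 0.875 + 0.393 × 0.607) / 0.268² = 7.849 × 0.3479 / 0.0718 = 38.02, rounded up to 39.
- Pooled variance gives 41; power at 39 is then 0.78.
- 39 / 0.80 = 48.75, rounded up to 49, if a 20% dropout is assumed.

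The figure reproduces. The concern does not depend on it, except that 39 and 49 serve as group sizes below.

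**4. Illustration on a continuous primary outcome such as RF-CSA change.** Normal approximation, two-sided alpha 0.05, SD = 1, positive values favour acupuncture, groups otherwise comparable.

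- Standard error at 39 per group: √(2/39) = 0.2265. At 49 per group: √(2/49) = 0.2020.
- Effect with 80% power at 39 per group: (1.960 + 0.842) × 0.2265 = 0.634 SD. This is taken as the assumed acupuncture effect.
- Let f be the extra exercise benefit as a fraction of that effect. Apparent effect = 0.634 × (1 − f). Power = Φ(apparent effect / SE − 1.960).

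| f (assumed) | Apparent effect (SD) | Power, 39 per group | Power, 49 per group |
|---|---|---|---|
| 0 | 0.634 | 0.80 | 0.88 |
| 0.25 | 0.476 | 0.56 | 0.65 |
| 0.50 | 0.317 | 0.29 | 0.35 |

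If acupuncture does nothing and the exercise benefit is 0, 0.159 or 0.317 SD, the apparent effect is 0, −0.159 or −0.317 SD. The chance of a significant result against acupuncture at 39 per group is Φ(benefit / 0.2265 − 1.960) = 0.025, 0.104 or 0.288.

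The protocol gives no exercise effect, so every value of f is an assumption.

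**The case against.** The strongest reply is that section 2.7 may only be describing, loosely, the exercise already in section 2.5.2. In-bed and wheelchair activities are what early exercise in an ICU ordinarily consists of, and the article is loosely worded elsewhere. On that reading the acupuncture group exercises too and the fault is one misplaced phrase. This is possible, and the acupuncture group is certainly not exercise-free. But nothing in the document gives that group the same prescription, and on this reading too the sentence needs correcting.

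Second, an active usual-care comparator is legitimate in a non-randomised pragmatic pilot, and any exercise benefit works against acupuncture, so it would not create a false claim of benefit. Both points stand. However, section 2.7 directs treatment by group and does not merely observe it, and an active comparator has to appear in the objective and the conclusion. A missed effect or a spurious harm would also mislead the larger study.

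Third, the numbers are hypothetical. That is correct: 0.634 SD is solved back from a group size derived from binary incidences, the fractions are assumed, and differences in who enters each group could offset or exceed any exercise effect. The figures show how the problem would act; they do not estimate its size.

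Fourth, the unseen tables or the full protocol may record exercise in both groups. That limits the point about checking it afterwards, but does not resolve the conflict between sections.

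**Conclusion.** The concern holds. Read as written, section 2.7 changes the comparison from basic care with or without acupuncture to acupuncture versus prescribed exercise, each on basic care. Objective 2 and the abstract do not say so, and the planned analysis cannot undo it.

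That the sections conflict is certain. The effect on the result is not: it depends on how much prescribed exercise adds to encouraged exercise, which the document does not say and which may be zero. Under the assumed fractions of 25% and 50%, power at 39 per group would drop from 80% to 56% and 29%. The point should be corrected because it determines what the trial can conclude.

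A separate, minor conflict: section 2.5.1 has the acupuncturist continue after ICU discharge until the 14-day course is finished, while section 2.8.7 rules out any intervention by the researcher after ICU discharge. It adds nothing to the weight of the main point.

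**What to change.** Choose one of three and word it consistently:

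- **Same exercise in both groups.** State in sections 2.5.2 and 2.7 that the exercise prescription applies equally to both. This preserves the contrast in the abstract and objective 2.
- **Exercise in controls only.** Keep section 2.7, and word the abstract, objective 2 and the conclusion as acupuncture versus prescribed exercise, each on basic care.
- **Section 2.7 only restates section 2.5.2.** Delete the phrase that places the exercise on top of basic treatment and refer to section 2.5.2 for both groups.

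In every case, record the exercise received in both groups if the case report form does not already do so. For the minor point, limit the sentence in section 2.8.7 to the time after the 14-day acupuncture course is completed.

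The cost is a wording change in a few sections and at most one case report form item. The sample size and the analysis methods do not change.
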